## Abstract

**Background:**

Patients with open fractures often experience complications during their injury. The treatments incur high costs. Interdisciplinary cooperation between different medical disciplines may improve treatment outcomes. Such cooperation has not yet been envisaged in the German health care system.

**Objective:**

The aim of the study is to improve the treatment of fractures with open soft tissue damage or postoperative complications in terms of duration and sustainability in a region in northwest Germany. Largely standardized diagnostics and therapy are intended to optimize processes in hospitals. In addition, a reduction in the duration of treatment and treatment costs is to be achieved.

**Methods:**

Using a digital platform, physicians from 31 hospitals present patient cases to an interdisciplinary group of experts from the fields of plastic surgery, infectiology, hygiene, and others. The group of experts from the environment of the University Hospital Münster promptly makes a joint treatment recommendation for the individual case. The plan is to examine 3300 patients with open fractures or surgical complications. As consortium partners, there are also 3 statutory health insurance companies. The extent to which the therapy recommendations are effective and contribute to cost reduction in the health care system will be empirically investigated in a stepped-wedge cluster-randomized design. In addition, medical and nonmedical professional groups involved in the project will be asked about their work in the project (in total, 248 clinic employees). The primary outcome is the complication rate of open fractures or the occurrence of postoperative complications. As secondary outcomes, the number of antibiotics administered, limb function, and quality of life will be assessed. The health economic evaluation refers to the costs of health services and absenteeism. For the work-related evaluation, workload, work engagement, work-related resources, readiness for technology, and ergonomic aspects of the new telemedical technology will be collected. In addition, clinic employees will give their assessments of the success of the project in a structured telephone interview based on scaled and open-ended questions.

**Results:**

The project started in June 2022; data collection started in April 2023. As of mid-June 2024, data from 425 patients had been included. In total, 146 members of staff had taken part in the questionnaire survey and 15 had taken part in the interviews.

**Conclusions:**

Standardized treatment pathways in the standard care of patients with open fractures and postoperative infections will be established to reduce complications, improve chances of recovery, and reduce costs. Unnecessary and redundant treatment steps will be avoided through standardized diagnostics and therapy. The interdisciplinary treatment perspective allows for a more individualized therapy. In the medium term, outpatient or inpatient treatment centers specialized in the patient group could be set up where the new diagnostic and therapeutic pathways could be competently applied.

**Trial Registration:**

German Clinical Trials Register DRKS00031308; https://drks.de/search/de/trial/DRKS00031308

**International Registered Report Identifier (IRRID):**

DERR1-10.2196/57820

## Introduction

### Background

Open fractures of the lower extremities are common, occurring with an incidence of approximately 11.5 per 100,000 [1]. Patients with open fractures often experience complications in the course of the disease, such as soft tissue infections, bone inflammation, defective bone fuse, and increased tissue pressure around the injury, with negative effects on blood supply and the nervous system [2,3]. Even for highly experienced service providers, it is often not possible to provide a sufficient quality of care for disciplines such as trauma, vascular and plastic surgery, infectiology, microbiology, and hygiene [4]. However, such interdisciplinary treatment has not yet been established in German primary and standard care. Currently, many patients with complicated or incorrectly healed fractures, infections, or chronically open wounds see several physicians in different hospitals, combined with inpatient transfers, redundant diagnostics, and long sick leave [5-7]. In many cases, the healing process is significantly impaired, and it is not uncommon for serious restrictions to remain.

In addition to the physical and psychological consequences for those affected, there are also the considerable costs of the health care system [1,8,9]. Patients with open lower-leg fractures incur almost twice as much cost (€11,000 [US $12,000]) as patients with closed fractures (€6600 [US $7100]) [5]. Open fractures with soft tissue infections lead to increased antibiotic use, additional surgeries, and longer hospital stays, which can increase costs 6-fold [5,10,11]. Against the backdrop of demographic change [12,13] as well as the increasing incidence of fractures due to comorbidities (eg, osteoporosis, gait uncertainty, and neurological diseases) and complications in the healing process from the age of 65 years onward, improving treatment options for complicated fractures and reducing the complication rate are of extreme importance [14]. Main complications that are encountered in this context are pseudarthrosis and chronic osteomyelitis. Pseudarthrosis is defined as a problem in fracture healing with missing consolidation of >6 months after trauma. Chronic osteomyelitis is a state in which destructive changes within the bone occur due to an infectious process. Both conditions prolong the healing process and usually make several surgical procedures necessary. In some cases, even an amputation must be considered.

In the United Kingdom, treatment structures have already been put in place to provide adequate and timely care to patients with these kinds of injuries. The British Orthopaedic Association and the British Association of Plastic, Reconstructive, and Aesthetic Surgeons introduced evidence-based standards of care for the treatment of severe, open lower-leg fractures (British Orthopaedic Association Standards for Trauma and Orthopaedics) [15]. It has been demonstrated that an early transfer of patients to specialized trauma centers and cooperation between surgical and nonsurgical disciplines significantly improve the course of treatment. Studies show a significant reduction in the infection rate, fewer additional surgeries, more successful limb reconstructions, and a reduction in treatment time [16-20].

Thus, concrete guidelines for the treatment of complicated fractures with soft tissue damage help not only improve the chances of treatment and healing but also reduce the costs of medical care. In particular, the involvement of an interdisciplinary team is essential for high-quality and cost-effective care [21]. In a joint interdisciplinary case conference, information and expertise can be exchanged, and treatment recommendations can be made based on broad expertise. This saves time and reduces redundant examinations and collisions of different treatment recommendations.

To consolidate treatment competence and ensure treatment quality, the standardization of specifications as well as diagnostic and treatment-related processes is essential. In the field of cancer therapy, interdisciplinary therapy recommendations have been established for decades within the framework of tumor boards. After intensive, interdisciplinary expert discussions, such a board makes a binding, patient-specific treatment recommendation considering all disease-relevant aspects [22].

So far, there is nothing comparable in Germany for the treatment of trauma to the extremities. In some large centers, there are interdisciplinary structures that deal with complex treatment situations. However, there is still no established process for the regular implementation of therapy steps. To date, there is also no way to standardize postoperative complications and treat them using stringent treatment pathways. Currently, people who have an open fracture or, in this context, a postoperative complication are admitted to the primary care clinic and treated on a monodisciplinary basis. The healing process of complicated fractures is further complicated by the fact that there are no contact points that take over the management of further treatment when the treatment options of a clinic for primary and standard care have been exhausted.

### Objectives

The aim of the EXPERT (Extremity Boards for process optimization, evaluation, risk minimization, and therapy optimization for fractures with soft tissue damage or postoperative infection of the lower extremities in the trauma network) project is to improve the treatment of fractures with open soft tissue damage or postoperative complications in northwest Germany rapidly and sustainably. Reductions in the duration and costs of treatment are further aims.

To achieve this, an interdisciplinary group of medical experts with a wide range of university expertise (eg, plastic surgery, infectiology, and hygiene) will make joint treatment recommendations within the framework of video case presentations. Consortium partners are 3 German statutory health insurance companies (BARMER, Techniker Krankenkasse, and AOK NordWest; see also Multimedia Appendix 1).

Physicians in standard care hospitals present their cases to the expert group (the Extremity Board) via telemedicine software and receive treatment recommendations tailored to the respective patients in a timely manner. In this way, the treatment result can be improved by adapting the individual therapy at an early stage.

On the basis of the knowledge gained in the Extremity Board, the interdisciplinary specialist group will define guidelines during the project to objectify decision-making paths, streamline processes, and define therapy algorithms. Through the close cooperation of the expert group with hospitals of primary and standard care, a joint agreement can be reached on treatment and documentation standards that relate to both the care of acute symptoms and postoperative complication management. The introduction of a web-based software platform enables both a secure exchange of medical information across the boundaries of different professional groups and the provision of interdisciplinary expertise in rural, structurally weak regions and regions affected by a shortage of specialists.

The effects of the new form of care based on the interdisciplinary approach and the associated standardization of diagnostics and therapy will be scientifically evaluated. Patient-related clinical success criteria as well as economic outcomes will be collected. As the new form of care has both content-related and organizational effects on the work in the clinics, work-related aspects will also be examined.

### Research Questions and Hypotheses

#### Clinical and Health Economic Hypotheses

It is assumed that efficient telemedical access to an interdisciplinary expert forum (the Extremity Board) with simultaneous therapy decisions in the treatment of fractures with open soft tissue damage and postoperative complications will achieve significant reductions in the length of inpatient stay, the total duration of treatment, and the complication and reoperation rate [23]. The measures optimize therapy pathways, standardize them, and make them more cost-effective. The establishment of the Extremity Board leads to higher guideline adherence, standardization, and documentation quality and, consequently, to reduced antibiotic consumption and a reduction in unnecessary diagnostics.

#### Work-Related Hypotheses

For the ergonomic evaluation of the EXPERT project, the job demands–resources (JD-R) model [24-26] on the influence of work resources and work requirements on work behavior will be used. In this theoretical model, which is backed up by a wide range of findings [27-29], work resources and work requirements are considered to be independent factors influencing work engagement and perceived stress from work. High cognitive, emotional, and physical demands such as time pressure, workload, complexity of tasks, and emotional stress lead to high demands, which has long-term negative consequences for employees and the company (eg, employee burnout, low job satisfaction, and low productivity [30]).

On the other hand, work resources such as social support, feedback, autonomy, and meaningfulness have a motivating effect because they satisfy basic needs for self-efficacy, attachment, security, and control [31,32]. Therefore, diverse work resources lead to more work engagement, which has positive consequences for employees and the company (eg, high job satisfaction and high productivity [30]).

The JD-R model also postulates that work requirements and work resources interact with each other, which affects the perception of stress and motivation. Thus, the availability of resources can mitigate the negative impact of the requirements. Resources seem to have a positive effect on motivation and work engagement, especially when work demands are high [33]. When work demands are high, employees increasingly perceive existing resources as helpful and useful, which helps them cope with the demands. This results in a subjectively lower burden (coping hypothesis [34,35]).

On the basis of the theoretical assumptions and empirical findings, the following hypotheses can be derived for the EXPERT project (Figure 1): (1) work requirements and workload increase in the intervention phase of the EXPERT project (hypothesis 1a); (2) work-related resources such as knowledge, competencies, and team support increase during the intervention phase (hypothesis 1b); and (3) the technical competence of employees increases during the intervention phase (hypothesis 1c).

Above- or below-average resources are recorded with the median of differences (pretest-posttest estimates of resources), leading to other hypotheses: (1) above-average resources are associated with lower workload, and below-average resources are associated with higher workload (hypothesis 2); (2) above-average resources are associated with higher work engagement (hypothesis 3a); (3) when resources increase, work engagement increases (hypothesis 3b); (4) if resources increase (exclusion of technical competence as a resource), then readiness for technology increases while the burden decreases (hypothesis 4a); (5) as technical competence (resource) increases, the burden decreases (hypothesis 5a); (6) when technical competence (resource) decreases, the burden increases (hypothesis 5b); and (7) above-average work engagement leads to higher readiness for technology, and below-average work engagement leads to lower readiness.

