Work resources are measured using the German-language questionnaire on resources and requirements in the world of work [54]. For the EXPERT project, 11 items are used, which relate to the resources “Leadership Support,” “Feedback,” “Peer-Support,” “Transparency,” “Diversity,” “Meaningfulness,” “Role Clarity,” “Learning Opportunity,” “Knowledge Management,” “Team Atmosphere,” and “Qualification.” All items are formulated as statements (eg, “I will be informed about all important content when implementing the new measures” [“transparency” resource]), which are rated on a scale from 1 to 6 (1=*not at all true*; 6=*completely true*).

Affinity for technology is measured using the German-language short scale for measuring readiness for technology [55]. It is a questionnaire with 12 items in the 3 scales “TB acceptance,” “TB control belief,” and “TB competence,” of which 9 items are used in this study. The item formulations have been adapted to the EXPERT project (eg, “I am very interested in the new telemedicine application” [acceptance scale], “It essentially depends on me whether I am successful in using the new telemedicine application” [control conviction scale], and “For me, dealing with technical innovations is usually too much to handle” [competence scale]).

The software ergonomics of the new telemedicine application are assessed using the German-language questionnaire Norm of the International Standard Organization 9241/10 [56,57]. On the basis of this instrument, software is evaluated regarding “adaptivity to requirements,” “comprehensibility,” “task appropriateness,” “ability to describe itself,” “fault tolerance,” “individualizable,” and “learning conduciveness.” The assessment of the 7 items is made on a bipolar scale based on symbols (from “– – –” to “+++”).

Finally, employees provide information about their profession (physician or nurse), whether they hold a management position (yes or no), and whether they already had experience in the use of telemedicine before the EXPERT project (yes or no).

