Ergonomic aspects of the telemedicine technology are collected and descriptively evaluated at the second measurement point in approximately half of the clinics.

As staff turnover in hospitals is high, it can be assumed that the groups of employees will be composed differently at each time of measurement. Therefore, no repeated-measure design can be applied. The analyses will be performed as balanced grouping factors with the same number of participants in all conditions (before vs after and treatment vs control). The measurements are considered as a grouping factor of a multiple ANOVA.

The evaluation of the repertory grids yields 2D representations of the negative and positive constructs mentioned by the interviewees during the interviews with respect to the different implementation steps, namely, preparation, development of new standards, interdisciplinary collaboration, and therapy implementation.

The combination of a questionnaire that can be used quickly and easily on a mobile phone and a telephone interview with both predetermined, scaled questions and open-ended evaluations according to the repertory grid technique results in a comprehensive picture of changes in pretest-posttest working conditions and of the success factors accompanying the process both in quantitative and qualitative terms. On the one hand, the web-based questionnaire before and after the introduction of the new form of care quantitatively captures influences on workload, work engagement, work-related resources, and readiness for technology and backs them up through the “difference-in-difference” design. On the other hand, central success factors regarding project implementation will be collected both quantitatively and qualitatively and made visible by means of the repertory grid technology as “mental maps” of the employees in the 31 participating clinics.

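### Above- and below-average resources are scored by pretest-posttest change, although hypotheses 2 and 3a speak of level, and the rule needs pairs of responses that the plan does not provide

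*Protocol article*

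**What the plan says.** In the protocol article, Work-Related Hypotheses, the scoring rule stands directly before the list of hypotheses that use it: "Above- or below-average resources are recorded with the median of differences (pretest-posttest estimates of resources".

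Two hypotheses in that list use the above/below-average grading of resources:
- Hypothesis 2: "above-average resources are associated with lower workload, and below-average resources are associated with higher workload (hypothesis 2".
- Hypothesis 3a: "above-average resources are associated with higher work engagement (hypothesis 3a".

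The next one is worded as change, with no reference to an average: "when resources increase, work engagement increases (hypothesis 3b". Hypotheses 4a, 5a and 5b also speak of increases or decreases. The theory set out earlier in the section says that "diverse work resources lead to more work engagement", which concerns having resources rather than gaining them.

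On measurement, the Questionnaires section says "For the EXPERT project, 11 items are used", each rated from 1 to 6. The work-related part of Data Analysis says that completed questionnaires are stored anonymously and that "it can be assumed that the groups of employees will be composed differently at each time of measurement". It concludes that a repeated-measures design is not possible, and it treats time as a between-groups factor in a 2 × 2 variance analysis (time by group).

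**The concern.** The authors distinguish level from change, since they list 3a and 3b separately. The only rule they give for the level groups is nevertheless a change score. If it is followed, the tests of hypotheses 2 and 3a relate workload and engagement to the gain in resources, and the result is labelled as an association with the amount of resources. The predictor of 3a then measures the same construct as the predictor of 3b, so the question about level has no test of its own.

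The same sentence has a second difficulty. It presupposes a before-and-after pair for each unit that is graded. The article does not say what that unit is, and for individual employees the Data Analysis section excludes such pairs.

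**Working it through.** **The plan's own figures.** The article gives no figure on how well the change split represents level. Its survey size reproduces (31 clinics × 8 = 248 questionnaires, or 31 × 4 = 124 per measurement time), but the point does not depend on it.

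**What the rule does on the 1-6 scale.** Take two units, which may be respondents or clinic means.
- Unit A scores 6 before and 6 after: difference 6 − 6 = 0.
- Unit B scores 2 before and 4 after: difference 4 − 2 = +2.

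B ranks above A on the difference, although A has more resources at both times. If the median difference lies between 0 and +2, A is graded below average and B above average. A positive median is in keeping with hypothesis 1b, which expects resources to rise in the intervention phase.

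**How far a change split departs from a level split (illustration).** Assumptions, none of them from the documents: linked pairs, bivariate normal scores, equal SDs before and after, pre-post correlation r. Let D = post − pre, with SDs set to 1.
- Var(D) = 2(1 − r) and Cov(D, post) = 1 − r, so corr(D, post) = √((1 − r)/2).
- By symmetry, corr(D, pre) = −√((1 − r)/2).
- Cov(D, mean level) = ½(Var(post) − Var(pre)) = 0, so corr(D, mean level) = 0.
- Two median splits with correlation ρ disagree in a share arccos(ρ)/π of units.

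| r | corr(D, post) | disagree with post level | disagree with pre level | disagree with mean level |
|---|---|---|---|---|
| 0 | 0.71 | 25.0% | 75.0% | 50% |
| 0.3 | 0.59 | 29.8% | 70.2% | 50% |
| 0.5 | 0.50 | 33.3% | 66.7% | 50% |
| 0.7 | 0.39 | 37.3% | 62.7% | 50% |
| 0.9 | 0.22 | 42.8% | 57.2% | 50% |

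If the ratio of posttest to pretest SD is allowed to run from 0.8 to 1.25, disagreement with the post level runs from about 22% to 57%. The 50% against the mean level then no longer holds exactly (about 35% to 65%).

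**Whether 3a and 3b become one test.** An illustrative simulation used 124 hypothetical linked pairs and 3,000 runs. Engagement at each time was 0.25 × resources + 0.7 × a stable personal component + 0.5 × noise. At r = 0.5:
- 3a, split on change against posttest engagement: significant in 24.1% of runs.
- 3a, split on posttest level against posttest engagement: 69.5%.
- 3b, change in resources against change in engagement: 97.4%.
- 3a (change split) and 3b gave the same verdict in 26.4% of runs.

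In this setting the change split loses much of a true level effect, but 3a and 3b do not give the same answer.

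**Whether the difference can be formed.** The rule needs a pretest and a posttest value for one unit. Anonymous storage, different staff at each time and the stated exclusion of repeated measures leave no individual pairs. A difference of clinic or group means is possible, but the rule does not say that this is meant.

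**The case against.** The strongest defence is that the sentence introduces a working term. Coming after hypothesis 1b, it may mean above-median gain, so that 2 and 3a concern a larger-than-typical gain and 3b any gain. The theory paragraphs are background and do not define the analysis variable, and the figure summarising the hypotheses is not available here. This reading is possible, but then 2 and 3a are worded wrongly and 3a shares its construct with 3b. The section needs correcting either way.

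It can also be said that scoring detail belongs in an analysis plan. That would answer an omission, but here the article states a rule, and the rule does not fit the hypotheses under it.

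Two objections to stronger readings stand in full. A reader might infer that about a third of employees will be put in the wrong group. That figure requires r = 0.5, equal SDs, normality, the post level as reference and linked individuals; the documents fix none of the first four, and the plan rules out the last. A reader might also infer that 3a and 3b become the same test. They do not: 3a as worded sets a median split against a level of engagement, while 3b sets an increase against an increase, so both cut-point and outcome differ.

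Finally, the stated 2 × 2 analysis does not use this split, so the main survey comparisons (hypotheses 1a to 1c) are untouched.

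**Conclusion.** The point holds as a mismatch between construct and score. The rule ranks change where hypotheses 2 and 3a speak of level. It can grade a unit with high, stable resources as below average, and it brings the predictors of 3a and 3b onto one construct. It also relies on pairs that the article excludes at employee level.

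The size cannot be taken from the documents. Under the assumptions shown, a change split disagrees with a post-level split in about 25% to 43% of units and is unrelated to the mean level (50%). These figures show that change is a poor stand-in for level; they do not forecast how many employees will be misclassified.

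The consequence is confined to the associational hypotheses of the work-related evaluation. The primary clinical outcome and the health economic analysis do not depend on it.

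**What to change.** In Work-Related Hypotheses, define above- and below-average resources for hypotheses 2 and 3a by the resource score at the same measurement point as the outcome. This takes one sentence and needs no linkage or new data, because resources are part of the questionnaire at both times.

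For the change hypotheses (3b, 4a, 5a and 5b), state that differences are formed at clinic or group level, in line with the decision against repeated measures. This takes a second sentence. Clinic-level differences require that each questionnaire can be assigned to its clinic. The article describes links specific to measurement time, group and cohort, so this should be confirmed before the clinic is named as the unit.

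If above-median gain was intended all along, reword 2 and 3a as change hypotheses and say how 3a then differs from 3b.

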Before the clinics of cohort 1 start implementing the new form of care in project month 7 (Figure 2), both the clinic staff of cohort 1 (treatment group) and the clinic staff of cohort 3 (control group) will be examined with the EXPERT questionnaire in project months 4 and 5 (measurement time Pre). In project months 12 and 13, clinic staff from both cohorts will repeat the questionnaire (measurement time Post). The same procedure will be followed for cohort 2 and cohort 4, 3 and 9 months later, respectively. Project staff from UKM will recruit enough people in the individual clinics for the surveys. Interested employees in the clinics who are or will be involved in the project can find out more about the survey in advance by means of an information text. The UKM project staff receive a questionnaire link as a QR code from the Steinbeis project staff for the corresponding measurement time tailored to the corresponding group and cohort and send this QR code to a contact person in the clinics. The contact persons pass on the QR code to the participants, who scan it on their mobile phones and answer the questions. Participants are requested to do so as soon as possible after receiving the link. The completed questionnaires are automatically stored anonymously on the Steinbeis University server and later evaluated in summary form.

The UKM staff draw attention to the project-related interviews in the clinics that are already implementing the measures. Interested employees can find out more about the interviews by means of an information text and can contact the Steinbeis project staff to make an appointment for the telephone interview. They then receive an email from Steinbeis with the confirmation of the appointment, the interview questions, and the (renewed) promise that their email address and telephone number will be deleted after completion of the project. The transcripts of the telephone interviews are anonymized using a code. The content collected in the interviews will be evaluated in summary form, quantitatively, and qualitatively.

Regarding the topics of workload, work engagement, work-related resources, and readiness for technology, the main effects and interactions between measurement time (before vs after start of the Extremity Board) and group of measures (treatment vs control) are examined via variance analysis; the result is a 2 × 2 design with the factors time (before vs after) and group (treatment vs control group).

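### Work-related hypotheses defined by pre-post resource differences cannot be tested per respondent in anonymous, unlinked surveys, and the 2 × 2 ANOVA omits the clinic

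*Protocol article*

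**What the plan says.** All places are in the Protocol article.

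- **Work-Related Hypotheses** defines the resource classification: "Above- or below-average resources are recorded with the median of differences (pretest-posttest estimates of resources". Hypotheses 2 and 3a compare above-average with below-average resources. Others are worded as change, for example "when resources increase, work engagement increases (hypothesis 3b"; 4a, 5a and 5b likewise speak of resources or technical competence going up or down.
- **Data Analysis, Work-Related Evaluation** describes the data. On storage: "The completed questionnaires are automatically stored anonymously". On who answers: "it can be assumed that the groups of employees will be composed differently at each time of measurement". The conclusion drawn there is: "Therefore, no repeated-measure design can be applied". The link sent to each clinic's contact person is described as being "for the corresponding measurement time tailored to the corresponding group and cohort".
- **Questionnaires** lists three closing items: profession, management position and previous telemedicine experience.
- **The analysis** is a two-factor design, time by group, of which the plan says: "The measurements are considered as a grouping factor of a multiple ANOVA".
- **Study Design** randomizes hospitals (31 clusters in 4 cohorts). Cohorts 1 and 2 are the treatment group and cohorts 3 and 4 the control group.
- **Data Sampling, Work-Related Evaluation** plans 4 employees per clinic at each of two times, and at least 120 people per measurement point.

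**The concern.** A median split of differences needs units that each have a Pre and a Post value, and so does a test of whether engagement rises where resources rise. The data collection described does not supply such units at the level of the respondent. If this stands, the team will have to invent a substitute definition after seeing the data, and a block of stated hypotheses will be reported on a basis that nobody specified.

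The second issue concerns the hypotheses that can be tested (1a to 1c: workload, resources and technical competence increase in the intervention phase). Staff in one clinic share leadership, team atmosphere and information flow, which are among the things they are asked to rate. The stated ANOVA treats them as independent, although the clinic is the unit that was randomized.

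**Working it through.** **1. Which units have a pre-post difference?**

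- *Respondent.* Storage is anonymous, no linking code is described, different people are expected at each wave, and repeated measures are ruled out. Number of respondents with a computable difference: 0.
- *Group or cohort.* Differences of means can be computed, but there are only 2 groups or 4 cohorts. With 4 cohort values, a median split is 2 against 2. There are 4!/(2!·2!) = 6 allocations, so the smallest two-sided permutation p-value is 2/6 = 0.33. A rank correlation of resource change with engagement change has 4! = 24 orderings, so its smallest two-sided p-value is 2/24 = 0.083. Neither can reach 5%.
- *Clinic.* This would give up to 31 units. The described link (time, group, cohort) and closing items do not show that clinic is stored. They do not say that it is not.

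**2. The plan's own sample size.** With f² = η²/(1−η²), a noncentral F test with 1 numerator degree of freedom, α = 5% and 80% power, the required number per measurement point is 152 at η² = 0.05, 120 at η² = 0.0625 and 47 at η² = 0.15. The stated 120 is therefore reproduced inside the stated range, for independent respondents. The planned 31 × 4 = 124 per time and 31 × 8 = 248 in total are arithmetically correct. No allowance for clinic is visible. For a single-time group comparison, 120 × (1 + 3ρ) gives 138 at ρ = 0.05 and 156 at ρ = 0.10.

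**3. Type I error of the ANOVA without a clinic term.** Inputs: m = 4 staff per clinic and wave (Data Sampling); staff ICC ρ = 0.05 or 0.10, an **assumption**, because the 0.05 in the document belongs to the clinical outcome; c = correlation of a clinic's effect between the two waves, from 0 (drifts freely) to 1 (stable), also assumed.

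- Interaction (difference-in-difference): DE = 1 + (m−1)ρ − mρc = 1 + 3ρ − 4ρc
- Group main effect: DE = 1 + (m−1)ρ + mρc = 1 + 3ρ + 4ρc
- Type I error ≈ 2·[1 − Φ(1.96/√DE)]

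| Test | ρ | c | DE | Type I error |
|---|---|---|---|---|
| time × group | 0.05 | 1 | 0.95 | 4.4% |
| time × group | 0.05 | 0 | 1.15 | 6.8% |
| time × group | 0.10 | 1 | 0.90 | 3.9% |
| time × group | 0.10 | 0 | 1.30 | 8.6% |
| group | 0.05 | 0 | 1.15 | 6.8% |
| group | 0.05 | 1 | 1.35 | 9.2% |
| group | 0.10 | 0 | 1.30 | 8.6% |
| group | 0.10 | 1 | 1.70 | 13.3% |

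A simulation of the stated ANOVA (20,000 runs, 16 against 15 clinics, 4 staff per clinic and wave) agrees. For the interaction it gives 4.5% to 6.8% at ρ = 0.05 and 3.9% to 8.6% at ρ = 0.10. For the group effect it gives 6.9% to 9.1% and 8.8% to 13.3%. The interaction formula gives DE = 1 when 3ρ = 4ρc, that is c = 0.75; in the simulation the error is close to nominal at c = 0.8.

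**The case against.** Four points can fairly be made against this.

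- *The unit is not named.* The hypotheses section does not say that each employee is split on his or her own difference, so a reader should not infer that no difference of any kind can be computed. This stands: group and cohort differences exist. They do not rescue the hypotheses, because 2 or 4 units are too few. The last hypothesis in the list, on above-average work engagement, needs no resource difference and is not affected.
- *Clinic may be recorded.* A condensed article can omit a clinic field. A reader might infer that clinic-level change is impossible; the text does not support that, because it is silent. What can be said is that the described link and items do not show it.
- *An analysis plan could add a clinic term.* It could, if clinic is stored. But the article names the two factors and the ANOVA, and no analysis plan can restore links between anonymous respondents.
- *The larger error rates belong to the less relevant test.* A reader might take 9% to 13% as the error of the intervention tests. That is not supported. Those figures are upper ends for the group main effect with clinic effects fully stable over time. The effect of interest is the interaction, whose error can fall on either side of 5%.

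**Conclusion.** The contradiction is real. Hypotheses 2 and 3a (through the median split) and 3b, 4a, 5a and 5b (through change) cannot be tested at respondent level with the data collection described, and the aggregates that are certain to exist are too few. This rests on the text alone and needs no numerical assumption.

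Hypotheses 1a to 1c remain testable through time × group. Leaving out the clinic puts the type I error of that test at about 4% to 9% for an assumed staff ICC of 0.05 to 0.10: conservative if clinic effects are stable between waves, liberal if they drift. The group main effect is anticonservative, up to about 9% (ICC 0.05) or 13% (ICC 0.10). The document gives no staff ICC, so these are ranges under an assumption; with an ICC of zero the ANOVA would be correct.

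The point concerns the staff evaluation only and leaves the primary clinical outcome untouched. It should be corrected, because part of a stated set of hypotheses has no valid test as written.

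**What to change.** 1. **Restate the resource hypotheses.** Test them as cross-sectional associations using the continuous resource score in place of the median split. Where clinic is known at both waves, they can instead be defined on the clinic mean, Post minus Pre. The cost is wording only, but a cross-sectional association no longer supports a statement about change.
2. **Confirm whether clinic is recorded.** If it is not, issue a separate link or code per clinic for the remaining waves. By 13 June 2024, 146 people had taken part against 248 planned responses, so about 248 − 146 = 102 were outstanding. A code added only at Post gives no clinic change where Pre had none; those clinics stay with the cross-sectional form.
3. **Have the code reviewed for data protection first.** With 4 staff per clinic and wave, clinic combined with profession and management position could identify individuals in the stored file, so a rule against reporting clinic results is not enough on its own. The review takes time and may need an ethics notification.
4. **Change the model.** Where clinic is available, fit time, group and time × group in a mixed model with a clinic random effect, adding clinic-by-time if it can be estimated. This costs only analysis wording.
5. **Where clinic is not available,** report the ANOVA with the limitation stated, and show the interaction result under a range of design effects, for example the 0.90 to 1.30 found above.
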